**FMD measurement before and after 20 minutes ischemia**

Participants will rest in the supine position in a temperature controlled room (22 °C) for at least 15-minutes to facilitate baseline assessment of heart rate and blood flow. To examine brachial artery FMD, the right arm will be extended and positioned at an angle of ~80° from the torso. A rapid inflation and deflation pneumatic cuff (D.E. Hokanson, Bellevue, WA) will be positioned on the forearm immediately distal to the olecranon process to enable induction of forearm ischemia. A 10-MHz multi-frequency linear array probe attached to a high resolution ultrasound machine (T3000; Terason, Burlington, MA) will be used to image the brachial arteries in the distal 1/3rd of the upper arm. When an optimal image is obtained, the probe will be held stable and the ultrasound parameters are set to optimize the longitudinal, B-mode images of lumen-arterial wall interface. Continuous Doppler velocity assessment will be simultaneously obtained using the ultrasound machine, and will be collected using the lowest possible insonation angle (always <60°), which will not vary during each study. Baseline images are recorded for 1 minute. The forearm cuff will be then inflated (>200 mmHg) for 5-minutes. Diameter and blood flow recordings will be resumed 30 seconds prior to cuff deflation and continued for 3 minutes thereafter. The baseline FMD measurement will be followed by the experimental IR-injury. The pneumatic cuff will be placed proximally around the upper arm and inflated to 200mmHg to apply 20 minutes of ischemia followed by cuff deflation. After 20 minutes of reperfusion, the procedures for FMD assessment as described above are repeated by the same experienced sonographer.

**Caffeine experiment:**

The FMD measurements will be preceded by a caffeine-infusion (4 mg/kg body weight intravenously over 10 minutes) 15 minutes before the IR intervention.

In both studies, blood will be drawn immediately before the first FMD measurement for the determination of the plasma metformin and caffeine concentration.

[figure not shown]

#### 4. STUDY POPULATION

##### 4.1 Population (base)

- Healthy volunteers (m/f)

##### 4.2 Inclusion criteria

- Age 30-50 years
- Written informed consent

##### 4.3 Exclusion criteria

- Smoking
- Hypertension (in supine position: systolic BP > 140 mmHg, diastolic BP > 90 mmHg)
- Hyperlipidaemia (fasting total cholesterol > 5.5 mmol/L or random > 6.5 mmol/L)
- Diabetes Mellitus (fasting glucose > 7.0 mmol/L or random glucose > 11.0 mmol/L)
- History of any cardiovascular disease
- Concomitant use of medication
- Renal dysfunction (MDRD < 60 ml/min)
- Professional athletes

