### 3. STUDY DESIGN

After written informed consent all healthy volunteers will undergo medical screening consisting of a short interview, physical examination, laboratory evaluation (glucose, cholesterol, kreatinine) and EKG. Females using oral contraceptives will be asked to continue their contraceptive throughout the study to maintain stable hormone levels. Females not on oral contraceptives will be measured at identical times in their menstrual cycle. As this is a cross-over model and subjects are their own control, potential differences in baseline FMD are not to be expected to influence results. For both trials, volunteers eligible for trial participation will receive study medication and instructions how to use it. The first study is a randomized, single-blinded cross-over study. 26 participants will be recruited and half of the participants will be pretreated with metformin 500 mg three times a day for 3 days, to ensure a steady state plasma concentration, whereas the other half will receive no medication. The two experiments will be separated by approximately two weeks to prevent any cross-over effect of metformin. The last dose of metformin will be given approximately 3 hours before the experiments. The FMD measurements will be performed, by an operator blinded for pretreatment after an overnight fast and 24 hours of caffeine abstinence (since caffeine is an adenosine receptor antagonist). Also, the participants have to refrain from strenuous exercise for at least 24 hours before the experiment, as this potentially act as a preconditioning stimulus. Experiments will be performed in a temperature-controlled room (22° C) and according to recent guidelines for assessment of the FMD. Measurements will always be performed at the same time of day to prevent diurnal variation in the FMD response.

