### 6.4 Summary of known and potential risks and benefits

Metformin is registered as a first-line treatment of patients with type 2 diabetes mellitus, and is the most widely prescribed antihyperglycemic drug worldwide. As mentioned previously, large prospective epidemiological studies have shown that treatment with metformin reduces total and cardiovascular mortality compared to alternative antihyperglycemic drugs. The most common side-effects are gastro-intestinal complaints, including nausea, bloating, abdominal pain and diarrhea. These complaints are usually mild and self-limiting. Lactic acidosis is a rare, but serious complication of metformin use, with an estimated incidence of 1-5 cases per 100.000 patient years, occurring mainly during metformin accumulation in the setting of chronic metformin use. In addition, it has

been suggested that metformin-induced lactic acidosis only occurs in the setting of other predisposing factors for lactic acidosis, such as renal dysfunction, hepatic dysfunction, of tissue hypoxia. In the absence of these alternative risk factors (i.e. in the case of acute overdose), metformin only induces life-threatening lactic acidosis in the presence of very high plasma concentrations of metformin. Lactic acidosis is therefore not to be expected in case of healthy volunteers.

Caffeine will be given in a dose comparable to 2-3 cups of regular coffee. In this dose, the blood pressure will increase modestly. We have used this dose in many previous studies as a tool to effectively block adenosine receptors, and this dose is not expected to give any unwanted side-effects.

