### 7.3 Study procedures

#### Enrollment check:

At entry of this study all volunteers will undergo an enrolment check consisting of a medical interview and physical examination performed by a qualified physician. EKG and venous puncture will be performed for some screening lab tests (total cholesterol, renal function (creatinine) and glucose). Just before the FMD measurement, a venous puncture will be performed for the determination of caffeine and metformin concentration.

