### 8.2 Adverse and serious adverse events

Adverse events are defined as any undesirable experience occurring to a subject during the study, whether or not considered related to the investigational drug. All adverse events reported spontaneously by the subject or observed by the investigator or his staff will be recorded.

A serious adverse event is any untoward medical occurrence or effect that at any dose:

- results in death;
- is life threatening (at the time of the event);
- requires hospitalisation or prolongation of existing inpatients' hospitalisation;
- results in persistent or significant disability or incapacity;
- is a congenital anomaly or birth defect;
- is a new event of the trial likely to affect the safety of the subjects, such as an unexpected outcome of an adverse reaction, lack of efficacy of an IMP used for the treatment of a life threatening disease, major safety finding from a newly completed animal study, etc.

All serious adverse events will be reported to the sponsor of this trial: Prof. [name], head of the department of Pharmacology and Toxicology. He delegates the appropriate handling of these events to the coordinating and principle investigators of this trial: Prof. dr. [name] and Dr. [name], Further report of these adverse events will be performed according to GCP as outlined below.

All SAEs will be reported through the web portal *ToetsingOnline* to the accredited METC that approved the protocol, within 15 calendar days after the sponsor has first knowledge of the serious adverse reactions.

SAEs that result in death or are life threatening should be reported expedited. The expedited reporting will occur not later than 7 calendar days after the responsible investigator has first knowledge of the adverse reaction. This is for a preliminary report with another 8 days for completion of the report.

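### The exclusion list omits pregnancy, and hepatic dysfunction, which section 6.4 names beside renal dysfunction, has neither a criterion nor a screening test

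*Protocol*

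**What the plan says.** Protocol section 4.1 defines the base population as "Healthy volunteers (m/f"), and section 4.2 adds only "Age 30-50 years" and written consent. Section 4.3 lists eight exclusions: smoking, hypertension, hyperlipidaemia, diabetes, cardiovascular history, concomitant medication, renal dysfunction and professional athletes. The organ-function item is "Renal dysfunction (MDRD < 60 ml/min").

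Section 3 foresees women both on and off oral contraception. Those on it are asked to continue. For the others, "Females not on oral contraceptives will be measured at identical times in their menstrual cycle".

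Screening is described twice with the same three blood measurements. Section 7.3 gives them as "screening lab tests (total cholesterol, renal function (creatinine) and glucose"), next to a medical interview, a physical examination and an EKG.

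Section 6.4 reports a suggestion that metformin-related lactic acidosis needs another predisposing factor, "such as renal dysfunction, hepatic dysfunction, of tissue hypoxia", and goes on to conclude that it is not expected in healthy volunteers. Section 10.4 repeats that conclusion and adds that neither drug is expected to harm participants. The Summary states that participants have no direct benefit.

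**The concern.** There are two separate gaps.

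The first is pregnancy. The label of healthy volunteer does not settle it, because pregnancy is not an illness. No criterion names it and no test looks for it, although the protocol plans for women of an age to conceive who use no oral contraceptive. At stake is an avoidable drug exposure in someone who gains nothing from it.

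The second is the liver. The protocol names hepatic dysfunction as a factor whose absence supports its safety conclusion, yet the criteria and the screen secure only the renal counterpart. At stake is whether eligibility delivers the population that the safety statement assumes.

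**Working it through.** No figure in the protocol bears on this point, so the check is a comparison of sections.

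**Pregnancy**

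1. Who may enter: both sexes (4.1), aged 30 to 50 (4.2).
2. Who among the women is expected: some not using oral contraceptives (3).
3. What would stop a pregnant woman: none of the eight items in 4.3, and none of the three blood measurements in 3 and 7.3. The interview and examination have no stated pregnancy criterion to apply.
4. What she would receive: in the cross-over, each participant takes metformin before one of the two experiments of the first study. On the stated schedule that is 3 doses a day × 3 days = 9 tablets of 500 mg. The second study adds a further course and caffeine infusions, but it runs only if the first shows protection (3).
5. When: a woman allocated to no medication first takes metformin only before her second experiment. Section 3 puts this approximately two weeks after the first, while its cycle rule implies about one cycle for women not on oral contraceptives. Either way, a single entry check would not cover the time between entry and that course.

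**Liver**

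| Factor named in 6.4 | Exclusion in 4.3 | Screening test in 3 and 7.3 |
|---|---|---|
| Renal dysfunction | MDRD below 60 ml/min | creatinine |
| Hepatic dysfunction | none | none |
| Tissue hypoxia | not named; the cardiovascular-history exclusion bears on it in part | none specific; interview, examination, EKG |

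Of the two organ dysfunctions named, one has both a criterion and a test and the other has neither.

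**A related contradiction**

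Section 4.3 excludes "Concomitant use of medication" without exception, whereas section 3 lets oral contraceptive users continue. Read literally, 4.3 would leave only women without oral contraception. The two sections must be reconciled, and the answer decides how many women the pregnancy gap concerns.

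**The case against.** The strongest reply is that healthy volunteers, seen by a qualified physician and excluded for any concomitant medication, would not include people with known liver disease. That stands. A reader might infer that 4.3 admits volunteers with liver disease in general; the protocol does not support this, and what remains is dysfunction that only a laboratory test would show. The label does not close that remainder. Section 4.3 itself spells out hypertension, hyperlipidaemia, diabetes, cardiovascular history and renal dysfunction, all of which the word healthy would arguably cover already.

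A reader might also infer that the safety case depends on an absence of hepatic dysfunction. It does not. Section 6.4 presents the predisposing-factor argument as a suggestion, and also cites a low incidence, occurrence mainly with accumulation in chronic use, and the need for very high plasma concentrations when other factors are absent. The Summary makes the same case without mentioning the liver. With the protocol's upper incidence of 5 per 100,000 patient-years, 26 participants × 3 days = 78 days, and 78/365 = 0.21 patient-years. The expected count is 0.21 × 5/100,000 ≈ 0.00001 for the first study, or about 0.00002 with both courses. This is indicative only: the rate does not describe people with hepatic dysfunction.

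Pregnancy plays no part in the lactic acidosis argument, so its omission does not undermine 6.4. It bears only on the general no-harm statements in the Summary and 10.4. Section 8.2 counts an event as serious if it "is a congenital anomaly or birth defect", but that is one item of a general definition and is no evidence that pregnancies are foreseen.

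For women off oral contraception, visits timed to the cycle make it implausible that a pregnancy would stay unrecognised through all four experiments. A reader might take two full courses and two caffeine infusions as the usual exposure; the realistic case is one course. For the same reason there is no validity argument: a woman to whom the cycle rule cannot be applied would not be scheduled. Cycle timing does not, however, prevent exposure before a pregnancy is recognised.

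Finally, the information letter and consent form are separate and not shown. They may mention pregnancy, so one cannot say that the trial ignores it. They would not change the list in 4.3.

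**Conclusion.** The point holds in a limited form. Section 4.3 is silent on pregnancy in a population where pregnancy is possible, and a healthy woman in early, unrecognised pregnancy passes every criterion as written. This is the weightier half. Independently, hepatic dysfunction is named as a risk factor in 6.4 but neither excluded nor tested for, so laboratory-only dysfunction would be missed. That removes one support from the safety statement and leaves the others standing.

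The plausible exposure is one three-day course per affected participant. The protocol gives no basis for the number affected, beyond that it is some fraction of 26. The primary comparison is not touched, and none of the sample size inputs in 4.4 depends on these criteria. The conclusion assumes that 4.2 and 4.3 are the full eligibility list. Eligibility belongs in the protocol, so a separate analysis plan would not fill the gap.

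**What to change.** Reconcile 4.3 and the 7.3 screen with 6.4 and section 3:

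- Add pregnancy and hepatic dysfunction to the exclusions in 4.3.
- Add a check of pregnancy status at entry to 7.3, and a liver enzyme measured in the screening blood already drawn. Make the matching change to the screening description in section 3.
- Have the sponsor set the hepatic threshold and decide whether and when the pregnancy check is repeated, since the metformin course may come well after entry.
- Reconcile the concomitant-medication exclusion with the continued use of oral contraceptives in section 3.

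The cost is two exclusion lines, one inexpensive pregnancy test, one extra assay on an existing sample and an occasional additional screen failure. The design and sample size do not change.

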##### 4.4 Sample size calculation

A recent study with a similar experimental design from our research group has reported that the FMD averages 7.7% before, and 5.1% after forearm IR. Therefore, the effect of IR

on FMD is 2.6% with a SD of 3.7%. However, this study did not have a cross-over design. A previous cross-over study from [name] et al. (unpublished results) has reported a Spearman correlation coefficient of 0.53 between the two paired FMD measurements, but in this study one of the FMD measurements was preceded by ischemic preconditioning. Thus, the correlation coefficient with two similar measurements of FMD is most likely stronger than 0.53. Assuming a correlation coefficient of 0.7, the expected SD of the effect of IR on FMD in our study therefore equals 2.85. With  $n = 26$  subjects, we will be able to detect a difference of 1.65% with a power of 80% and a type I error probability of 5%, which is a relevant difference.

## 5. TREATMENT OF SUBJECTS

### 5.1 Investigational product/treatment

In the first study, patients will be randomized to either metformin 500mg three times a day for 3 days before experiments. Participants are not allowed to drink caffeine containing beverages starting 24 hours prior to measurements.

In the second study, the subjects will also be pre-treated with metformin or no medication before each of the two experiments, and will all receive caffeine (4 mg/kg iv in ten minutes) 15 minutes before the experiment.

### 5.2 Use of co-intervention (if applicable)

Not applicable.

### 5.3 Escape medication (if applicable)

Not applicable.

## 6. INVESTIGATIONAL MEDICINAL PRODUCT

### 6.1 Name and description of investigational medicinal product(s)

Metformin is an antihyperglycaemic drug that reduces plasma glucose levels in patients with diabetes mellitus by improving insulin sensitivity, which results in a reduced hepatic glucose production and improved peripheral glucose uptake. Metformin is registered in the Netherlands as a first-line treatment of patients with type 2 diabetes mellitus.

Caffeine is the most widely consumed drug worldwide, and acts as a nonselective adenosine receptor antagonist. The dose of 4 mg/kg is equivalent to the dose in 2-3 cups of regular coffee.

### 6.2 Summary of findings from non-clinical studies

In murine models of myocardial infarction, the administration of metformin (in a dose comparable to the dose normally used to treat patients with type 2 diabetes mellitus), either before ischemia or immediately at the moment of reperfusion, profoundly reduced myocardial infarction with approximately 50%

### 6.3 Summary of findings from clinical studies

Large epidemiological trials have reported that patients with type 2 diabetes mellitus who were treated with metformin had a lower total and cardiovascular mortality than patients treated with alternative glucose-lowering drugs, despite similar glycaemic control. In addition, a retrospective analysis of the Prevention of Restenosis with Tranilast and its Outcomes Trial (PRESTO) showed that the use of metformin reduced death and myocardial infarction in diabetics undergoing coronary interventions, compared with diabetic patients treated with alternative glucose-lowering drugs.

### 6.4 Summary of known and potential risks and benefits

Metformin is registered as a first-line treatment of patients with type 2 diabetes mellitus, and is the most widely prescribed antihyperglycemic drug worldwide. As mentioned previously, large prospective epidemiological studies have shown that treatment with metformin reduces total and cardiovascular mortality compared to alternative antihyperglycemic drugs. The most common side-effects are gastro-intestinal complaints, including nausea, bloating, abdominal pain and diarrhea. These complaints are usually mild and self-limiting. Lactic acidosis is a rare, but serious complication of metformin use, with an estimated incidence of 1-5 cases per 100.000 patient years, occurring mainly during metformin accumulation in the setting of chronic metformin use. In addition, it has

been suggested that metformin-induced lactic acidosis only occurs in the setting of other predisposing factors for lactic acidosis, such as renal dysfunction, hepatic dysfunction, of tissue hypoxia. In the absence of these alternative risk factors (i.e. in the case of acute overdose), metformin only induces life-threatening lactic acidosis in the presence of very high plasma concentrations of metformin. Lactic acidosis is therefore not to be expected in case of healthy volunteers.

Caffeine will be given in a dose comparable to 2-3 cups of regular coffee. In this dose, the blood pressure will increase modestly. We have used this dose in many previous studies as a tool to effectively block adenosine receptors, and this dose is not expected to give any unwanted side-effects.

### **6.5 Description and justification of route of administration and dosage**

The subjects will be treated with 500 mg of metformin three times a day for 3 days before experiments. To ensure a peak plasma metformin concentration at the moment of experiment, the last dose will be administered approximately 3 hours before start of experiment ( $T_{max}$  of metformin is 3 hours).

Caffeine will be given in a dose of 4 mg/kg intravenously over ten minutes. We have previously shown that this dose results in a plasma concentration that is comparable to the concentration after drinking 2-3 cups of regular coffee, and that this concentration effectively blocks the adenosine receptors involved in protection against IR-injury.

### **6.6 Dosages, dosage modifications and method of administration**

Metformin tablets of 500 mg three times a day during 3 days.

### **6.7 Preparation and labelling of Investigational Medicinal Product**

Tablets containing metformin 500 mg will be provided by the department of Clinical Pharmacy of the Radboud University Nijmegen Medical Centre according to GMP-standards. These medicinal products will be stocked at the department of Clinical Physiology at the RUNMC at a controlled temperature (15-25° C).

Caffeine will be obtained from the department of Clinical Pharmacy (ampuls of 5 ml containing 10 mg/ml) and dissolved in 100 ml of saline.

### **6.8 Drug accountability**

The department of Clinical Pharmacy of the Radboud University Medical Centre will provide the metformin used in this trial. The products are transported to the department of Clinical Physiology at the RUNMC and stored there under GMP conditions. Compliance to the treatment with metformin will be checked by pill counting. The completed drug accountability of all involved medicinal products will be documented by the investigator on specially designed drug accountability form.

## 7. METHODS

### 7.1 Study parameters/endpoints

#### 7.1.1 Main study parameter/endpoint

Difference in flow mediated dilation before and after 20 minutes of forearm ischemia and reperfusion.

#### 7.1.2 Secondary study parameters/endpoints (if applicable)

Not applicable.

#### 7.1.3 Other study parameters (if applicable)

Baseline screening (BMI, blood pressure, glucose, renal function).

